**Figure 1 F1:**
[figure not shown]
Inclusion and exclusion criteria for participants. SUD, Substance use disorder; ICD-10: F10-19 = International Classification of Diseases-10: F10-F19: Mental and behavioral disorders due to psychoactive substance use; ATC, Addiction treatment center; HIIT, High-intensity interval training.

**Figure 2 F2:**
[figure not shown]
Study flow chart. HIIT, High-intensity interval training; TAU, Treatment as usual; 1 = for intervention: unable to complete/discontinuation (e.g. sick, relapse), missing data; for follow-up periods: unable to contact after ended treatment.

We intend to store participant data for analyses until 2025 and will keep them anonymized for another five years. We will handle all participant data coded with an identification-number, which links the participant to a list of names. This list will be stored as an encrypted data file on a data server belonging to St. Olavs University Hospital, and only the project leader and the responsible research coordinator will have access to this list. We will use the identification-number for all assessments, tests, and analyses of the data throughout the whole project. The Regional Committee for Medical Research Ethics, Norway, has approved the protocol and procedures. We registered the study at ClinicalTrials.gov in April 2022 (Identifier: NCT05324085).

### Assessments

2.2.

The participants will be assessed at baseline, after eight weeks of intervention, and at 3- and 12-months follow-up (Table 1). We will perform most assessments on two consecutive days: neuropsychological tests at test day one, and the fitness test and questionnaires at test day two. Blood samples will be collected on a separate day.

#### Neuropsychological tests

2.2.1.

Many patients with SUD suffer from impaired cognitive functioning, especially executive dysfunction, reduced response inhibition, attention, and working memory (9, 14, 46), which can influence treatment outcome negatively (10–12). A selection of standardized and validated neuropsychological tests and work tasks will be conducted to measure the extent of these impairments at baseline and follow-up time points. The following tests were chosen due to their applicability (easy to administer, time-efficient) and established validity and reliability in this patient population (5–7, 47).

##### BRIEF-A

2.2.1.1.

The BRIEF-A is a 75-item standardized questionnaire appraising executive functions in real-life situations (48). It incorporates self-reported cognitive characteristics and collects subjective information about the ability to maintain appropriate control of emotional responses and behavior. The BRIEF-A encompasses nine sub-scales in three indexes/composite scores: *inhibit, shift, self-monitor, emotional control* (Behavioral Regulation Index, BRI); *initiate, plan/organize, working memory, organization of materials, and task monitor* (Metacognition Index, MI); BRI and MI are also combined to an overall summary score (Global Executive Composite, GEC). It additionally includes three validity scales (i.e., negativity, inconsistency, and infrequency). Conducting BRIEF-A takes 10–15 min. All items are rated with a 3-point scale, whereas a total score ≥65 points is considered as a clinically significant executive function deficiency (48, 49). The BRIEF-A has been shown to be particularly sensitive for assessing executive functions in the SUD population, and is considered more relevant for real-life situations than performance-oriented measures of executive functions (e.g., memory tasks) (5, 50).

##### MoCA

2.2.1.2.

The MoCA is a brief screening tool to detect mild cognitive impairment (51), and is used in populations with different mental and cognitive health challenges, including SUD (6, 52). It is a performance-based test that can be administered in approximately ten minutes and assesses the following CF categories: *visuospatial/executive abilities*, *naming*, *memory*, *attention*, *language*, *abstraction*, and *orientation* (51). All categories range from 3 to 5 points each, leading to a maximal score of 30 points, whereas a score of <26 points is considered as having impaired CF (51).

##### Stroop test and working memory tasks

2.2.1.3.

We will use commercially available tests developed by *Cambridge Brain Science* (https://www.cambridgebrainsciences.com/). This web-based cognitive assessment platform delivers digital cognitive tests based on validated traditional neuropsychological tasks (e.g., original Stroop test, 1935 (53)). These computer-based tests are widely used and cited in scientific literature (54, 55). As opposed to more traditional pen-and-paper tasks, they have the advantage of being more interactive and dynamic due to the task's difficulty level automatically adjusting to the participant's performance (55).

We will conduct the tests “Double Trouble” (manual Stroop task), “Digit Span” and “Token Search” to assess *response inhibition* and *selective attention*, *verbal short-term/working memory*, and *spatial working memory*, respectively. Performing these tests takes approximately five minutes each. Outcome measures are number or accuracy of correct answers and response time (56).

#### Physical examination/tests

2.2.2.

##### Anthropometrics

2.2.2.1.

Before physical testing, body weight and height will be measured with a standard scale and a stadiometer (standing without shoes), respectively. Medical staff at the clinic will perform a general health check (e.g., assess blood pressure and resting heart rate) as a standardized part of patient care. The research staff will also retrieve this information from patient journals.

##### Exercise test

2.2.2.2.

Cardiorespiratory fitness will be measured as V˙O_2max_ (or V˙O_2peak_, if criteria for V˙O_2max_ are not fulfilled, see below) by cardiopulmonary exercise testing, which is regarded as the gold standard to determine aerobic fitness level (57). Maximal oxygen uptake will be assessed on a treadmill (TX200, Gymleco, Norway) using a metabolic gas analyzer (MetaLyzer 3B, Cortex, Germany). Participants will start with a 10-min warm-up at 5% incline, followed by an individualized test protocol. Here, we will increase either incline (1%–2%) or velocity (0.5–1 km · h^−1^) every minute until exhaustion. The mean of the highest oxygen uptake values measured during a 30 s interval is defined as V˙O_2max_. At least one of the following criteria will be used to verify V˙O_2max_: plateau in oxygen uptake despite increasing workload; respiratory exchange ratio > 1.05; blood lactate concentration >7 mmol (58). Blood lactate will be measured within one minute after the test (Biosen C_line, EKF Diagnostics GmbH, Barleben, Germany). Maximal heart rate (HR_max_) will be assessed by adding two beats per minute to the highest HR attained in the test (59), and will be used as a basis to calculate the workload for the HIIT sessions. Moreover, maximal effort during the test will be evaluated by Borg Rating of Perceived Exertion (RPE) scale (60).

##### Blood samples and immunoassays

2.2.2.3.

To add biological insight, we will analyze relevant biochemical markers of neuroplasticity and cognition. Our aim is to explore possible alterations in serum concentration of relevant biomarkers of neurocognition throughout the intervention. Qualified staff at Lade ATC will draw blood samples following an overnight fast, before and after the intervention, applying well-established and validated procedures. Serum samples will be stored at −80°C until further analysis. The serum concentrations of relevant proteins (e.g., BDNF, Klotho and Gpld1) will be assessed using enzyme-linked immunosorbent assay (ELISA) kits. Additionally, we will use multianalyte profiling (Milliplex MAP) assays to assess larger panels' neurocognitive inflammatory/metabolic markers. For storage and management of serum samples, we will use the services of Biobank1 (Regional Research Biobank St. Olavs Hospital, https://biobank1.no/nb/).

#### Other assessments

2.2.3.

##### Questionnaires

2.2.3.1.

We have developed a questionnaire that acquires information concerning substance use, craving, motivation, self-esteem, sleep quality, etc. with items put together from a carefully selected battery of well-established and validated questionnaires (61–73). For instance, the 10-item short form of the Hopkins Symptoms checklist (SCL-10) has been incorporated to measure psychological distress (63), and several items of World Health organization's Quality of Life questionnaire (WHOQOL-BREF) have been added to assess quality of life (73). Additionally, we will monitor PA level by administering the International Physical Activity Questionnaire (IPAQ, short version) (74).

##### Clinical status therapeutic hours and concomitant medication

2.2.3.2.

The research staff will register demographic data and medical history. Information concerning SUD diagnosis, comorbidities, therapeutic hours and previous treatment for SUD (if applicable) will be obtained from the patient journal by authorized staff at Lade ATC.

### Intervention

2.3.

#### Control group

2.3.1.

Participants will receive standard TAU by therapists at Lade ATC with specific competence in working with patients with SUD. The content of TAU is broadly individualized, but also includes various forms of group therapy, psychotherapy, psychoeducation and PA. The PA schedule for the patients typically includes gym-based exercises (e.g., yoga, different types of circuit training, team sports) and various outdoor activities (e.g., walks, hikes, bonfire), four times per week all together.

#### Exercise group

2.3.2.

Participants will undergo eight weeks of supervised aerobic HIIT, three times a week. This type of training is chosen since it earlier has been shown to be effective for improving somatic health in patients with SUD (41), and to have promising effects on CF as well (43, 75). The HIIT sessions will substitute most of the PA sessions included in TAU, and will be performed as 4 × 4 min intervals, running (or walking on steep incline) on a treadmill (see Figure 3 for illustration). The session will start with a 10-min warm-up at 60%–70% of HR_max_, followed by 4 × 4-min intervals at ∼90% of HR_max_, with 3-min active rest periods at approximately 60%–70% of HR_max_ between each interval, as described previously (41). The workload is relative to the maximal exercise capacity of each patient, and will be controlled using HR monitors (Polar Vantage M multisport watch and HR sensor H10, Polar Electro, Finland) and Borg scale derived RPE (60). We will instruct the participants to follow a RPE score of 16–18 (hard–very hard) for the interval period and 11–13 (fairly light–somewhat hard) for the warm-up, active rest periods, and cool-down. Total duration of each HIIT session is approximately 40–45 min.

**Figure 3 F3:**
[figure not shown]
High-intensity interval training protocol performed as 4 × 4 min intervals. HR_max_, Maximal heart rate.

### Feasibility and adherence

2.4.

Intervention periods of 8–12 weeks can be considered as a normal duration for this type of training intervention (16, 41, 76). The participants will only perform three short sessions per week for eight weeks, and the training facilities are situated on-site at the clinic, with immediate access to medical assistance if needed. In addition, qualified staff will supervise all training sessions, ensuring close monitoring and facilitating adherence to training. It has already been shown good adherence to HIIT sessions in this patient population (41), confirming the feasibility of this project. Moreover, participants will exercise together two by two, providing a social aspect for training which may enhance motivation to perform and adhere to the sessions. Sport therapists at Lade ATC will facilitate the implementation of the training sessions. The exercise tests and blood sampling may cause discomfort, but these assessments are usually well tolerated when performed by experienced staff following standardized protocols. However, adverse events as fatigue, increased stress, and anxiety may occur. Patient safety is highly prioritized and in case of suspicion of adverse events or reactions, we will terminate the intervention immediately and the patient will be taken care of by medical personnel.

### Sample size and statistical analyses

2.5.

The primary comparison is altered BRIEF-A score in aerobic HIIT + TAU vs. TAU alone after eight weeks of intervention. Based on previous studies highlighting the pronounced effect of aerobic exercise, preferably using high intensity (15, 77), we anticipate a feasible effect size of  ≥ 0.6 (Cohen's *d*) on BRIEF-A score favoring the HIIT intervention. With a statistical power of 0.8 and a significance level of 0.05, it will be sufficient with 45 participants in each group. To compensate for an expected dropout rate of approximately 20%, we aim to include 55 participants in each arm of the study (*n* = 110 patients in total). This sample size is feasible to recruit within 18 months, considering the annual patient flow at Lade ATC. It will also be possible to expand the recruitment phase, and subsequent intervention period and follow-up for another six months if necessary.

We will present descriptive data as mean ± standard deviation, and medians with 25th to 75th percentiles where appropriate. To compare mean change in BRIEF-A score between the two study groups, we will apply a two-level linear mixed model (LMM), with BRIEF-A score as dependent variable, time point as level 1 and participant as level 2. Group allocation and an interaction term between group allocation and time point will be included as covariates. The LMM analyses will also produce unbiased estimate when data is missing for some time points under the assumption that the data is missing at random (78). We will perform the analysis according to the intention-to-treat principle, including all randomized study participants regardless of adherence. A per-protocol analysis of the primary outcome will also be performed, including all participants adherent to at least 70% of training sessions (i.e., 17 out of 24). We will perform similar analyses for other biological and neuropsychological parameters, as well as self-report questionnaires (secondary endpoints). In sensitivity analyses we will adjust for baseline values of cardiorespiratory fitness (27), and psychological distress (i.e., SCL-10 total score) (6). Executive dysfunction is a common feature in attention-deficit/hyperactivity disorder (ADHD), anxiety and mood disorders (79, 80), and due to high co-occurrence of those disorders among patients with SUD (81, 82), these will also be adjusted for. Statistical significance will be set to an *α*-level of *p* < 0.05, and effect sizes (i.e., Cohen's *d* (83)) will be presented together with 95% confidence intervals. We will use the software program SPSS (version 25.0 or higher) and GraphPad Prism (version 5.0 or higher) for all statistical analyses.

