### Blinding

2.6.

Due to the nature of the study being an interventional trial with supervised training sessions, the study investigators and participants will not be blinded to group allocation. However, we will undertake baseline assessments prior to randomization.

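### The primary mixed model leaves the arms' baseline BRIEF-A means free to differ, so the week-8 contrast is valid but less precise than the trial's own data allow

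*Protocol article*

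**What the plan says.** Section 2.5 of the protocol article states the purpose of the primary analysis: "To compare mean change in BRIEF-A score between the two study groups". The tool is a two-level linear mixed model, "with BRIEF-A score as dependent variable, time point as level 1 and participant as level 2". The group terms are then named: "Group allocation and an interaction term between group allocation and time point will be included as covariates".

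Section 2.2 gives the visits: "The participants will be assessed at baseline, after eight weeks of intervention, and at 3- and 12-months follow-up". Table 1 marks BRIEF-A at all four. Section 2.6 adds that "we will undertake baseline assessments prior to randomization".

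The baseline adjustments named in section 2.5 are for other variables: "In sensitivity analyses we will adjust for baseline values of cardiorespiratory fitness (27), and psychological distress", and also comorbid ADHD, anxiety and mood disorders. Nowhere are the arms' baseline BRIEF-A means set equal, and nowhere is baseline BRIEF-A used as a covariate.

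On sample size, section 2.5 expects an effect of at least 0.6, expressed as "Cohen's *d*) on BRIEF-A score favoring the HIIT intervention", and concludes: "With a statistical power of 0.8 and a significance level of 0.05, it will be sufficient with 45 participants in each group". It does not say whether the SD behind d is that of the score or of its change.

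**The concern.** With baseline among the outcome rows, a group main effect beside the group-by-time interaction gives each arm its own baseline mean. The interaction at week 8 is then the between-arm difference in change from baseline.

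Because baseline precedes randomisation, any baseline difference between the arms is chance. The planned model spends information estimating a difference whose true value is zero, and it subtracts the whole observed baseline difference from the week-8 difference. A model with one common baseline mean subtracts only the part that the baseline to week-8 correlation supports.

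At stake is precision on the single primary contrast, and how far the estimate moves when the arms differ by chance at baseline. Section 2.5 also applies similar analyses to the secondary outcomes, so the loss recurs there.

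**Working it through.** **Inputs from the document (sections 2.2, 2.5, 2.6).** d = 0.6; power 0.80; α = 0.05; 45 per group after dropout, 55 randomised per arm; expected dropout about 20%; BRIEF-A at four visits; baseline before randomisation.

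**Assumed, not in the document.** ρ, the baseline to week-8 correlation of BRIEF-A, taken from 0.3 to 0.7; equal score variance σ² at each visit; time as a categorical fixed effect, which the model description does not list in so many words.

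**Step 1: the plan's own figure.** A two-sided two-sample t-test with d = 0.6, α = 0.05 and power 0.80 needs 44.6 per group, rounded up to 45; power at 45 is 0.804. The stated 45 reproduces, and it does not rely on any baseline adjustment.

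**Step 2: variance of the week-8 contrast, complete data.** Per participant:
- difference in raw change (planned model): 2(1−ρ)σ²
- common baseline mean, or adjustment for baseline: (1−ρ²)σ²
- ratio: 2(1−ρ) / [(1−ρ)(1+ρ)] = 2/(1+ρ)

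This is 2/1.3 = 1.54 at ρ = 0.3, 2/1.5 = 1.33 at ρ = 0.5, and 2/1.7 = 1.18 at ρ = 0.7. At ρ = 0.9 it is only 1.05.

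**Step 3: check by fitting both models.** Random-intercept models were fitted to simulated trials (four visits, 55 per arm, 150 runs per setting), with and without the group main effect.
- Complete data: the planned model's week-8 interaction equalled the raw difference in mean change to within 6 × 10⁻¹⁵. The model-based variance ratio was 1.335 at ρ = 0.5 and 1.176 at ρ = 0.7.
- 20% lost at random after baseline: the estimate stayed close to raw change (correlation 0.97 to 0.98), and the model-based ratios fell to 1.27 and 1.14. The empirical ratios were lower (1.22 and 1.06), but are noisy with 150 runs.
- The two models' mean estimates agreed in every setting (for example −0.563 and −0.566 at ρ = 0.5 with dropout). The difference is one of precision, not bias.

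**Step 4: power at 45 per arm, complete data, under both readings of d.** If d is in SDs of the score, the effective d is 0.6/√(2(1−ρ)) for the planned model and 0.6/√(1−ρ²) for the constrained one. If d is in SDs of change, it is 0.6 for the planned model and 0.6 × √(2/(1+ρ)) for the constrained one.

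| ρ | d in score SDs: planned | d in score SDs: constrained | d in change SDs: planned | d in change SDs: constrained |
|---|---|---|---|---|
| 0.3 | 66% | 84% | 80% | 94% |
| 0.4 | 73% | 87% | 80% | 92% |
| 0.5 | 80% | 90% | 80% | 90% |
| 0.7 | 95% | 98% | 80% | 86% |

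At ρ = 0.5 the constrained model needs about 33 per group where the planned one needs 44 (normal approximation).

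**Step 5: sensitivity to chance imbalance.** With 45 per arm the standard error of the baseline difference is √(2/45) = 0.21 score SDs. The planned and baseline-adjusted estimates differ by (1−ρ) times the observed baseline difference. At ρ = 0.5, an imbalance of one standard error moves them 0.5 × 0.21 = 0.105 SD apart, or 0.105/0.6 = about 18% of the planned effect if d is in score SDs.

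**The case against.** The planned model is a standard one and estimates what the article says it wants, a between-arm difference in mean change. A reader might infer from the free baseline term that the primary analysis is biased or that its type I error is wrong. Neither follows: baseline precedes randomisation, so over repeated randomisations the estimate is unbiased and the test is valid. The over-correction for imbalance in step 5 is conditional on the imbalance that happens to be observed.

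A reader might also infer that the baseline score is thrown away. It is not; it is subtracted. Relative to comparing week-8 scores alone (variance σ²), raw change at ρ = 0.7 brings the variance to 0.60σ², against 0.51σ² with adjustment, which is 0.40/0.49 = 82% of the available gain. Only at ρ = 0.5 is that gain nil, and only below 0.5 is raw change worse than ignoring baseline.

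Nor do the documents support calling the trial underpowered. A shortfall needs two things they do not state: that d is in SDs of the score, and that ρ is below about 0.5. If d is in SDs of change, the stated 80% holds whatever ρ is.

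Finally, the absence of baseline BRIEF-A from the sensitivity covariates is not a separate defect. It is already an outcome row, and adding it as a covariate to the same model would not be a sound remedy.

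All of this stands. What remains is that section 2.5 names the group terms explicitly, that nothing elsewhere constrains the baseline means, and that the constrained model gives higher power under either reading of d at every ρ tabulated.

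**Conclusion.** The point holds as one of efficiency and of sensitivity to chance imbalance, not of validity. The planned week-8 contrast is essentially the difference in raw change. Its variance exceeds that of a common-baseline model by about 33% at ρ = 0.5 and 18% at ρ = 0.7 with complete data, and by about 27% and 14% in simulation with 20% dropout.

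The reading of the model is secure, subject to time being categorical. The size is less so: it depends on ρ, which is not given, and the consequence for power depends on which SD d refers to, which is also not stated. The gain shrinks as ρ rises. It is an improvement worth making because it is free, not because the plan as written would mislead.

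**What to change.** Replace the sentence on the group terms. Fit the linear mixed model to BRIEF-A at all four visits with categorical time and group-by-time terms at the post-baseline visits only, and no group main effect, so that the arms share one baseline mean. The primary estimate is the group term at week 8; with a common baseline mean it is still the between-arm difference in mean change. All randomised participants with a baseline score stay in the model, in keeping with the intention-to-treat statement in section 2.5. Use the same form for secondary outcomes that have a baseline value.

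An alternative is to model post-baseline scores only, with baseline BRIEF-A and its interaction with time as covariates. Precision is similar, but participants with no post-baseline score drop out, so the two are not interchangeable when about 20% are expected to be lost.

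It would also help to state which SD d = 0.6 refers to, and the ρ assumed.

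Cost: a sentence or two of analysis wording; no new data and no extra participants.

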**Aim**

The overall aim of this project is to investigate the effect of HIIT on CF and associated mechanisms, and the subsequent effect on treatment outcome in patients with SUD.

*Primary aim*
•Assess the change in executive function between an intervention group (HIIT + treatment as usual (TAU)) and a control group (TAU) after eight weeks of intervention. Executive function will be assessed using the neuropsychological test BRIEF-A (Behavior Rating Inventory of Executive Function-Adult, self-report version). This test has been established as a valid and reliable assessment of executive functions in patients with SUD (5, 6), and was therefore chosen as the primary endpoint of this study.*Secondary aims*
•Map CF in subgroups of patients with SUD (e.g. type of substance, age, fitness level).•Change in other neuropsychological assessments (i.e. Montreal Cognitive Assessment (MoCA), Stroop test, working memory tasks) between time points (Table 1).•Change in scores on self-report questionnaires (e.g. substance use, mental distress, sleep quality, quality of life, etc.) between time points (Table 1).•Assess compliance to TAU (e.g. therapeutic hours) and long-term outcome at follow-up (i.e. relapse rate).•Analyze exercise-induced responses of neurocognitive biochemical markers.

**Table 1 T1:** Overview of time points of measurements.

	Pre-intervention	Intervention (eight weeks)	Post-intervention	3-months follow-up	12-months follow-up
Demographic information	x				
Patient journal*	x		x		
Concomitant medications	x	x	x		
Adverse events		x			
Physical examination/test	x		x		
– Anthropometrics – Blood sample – V˙O_2max_-test					
Neuropsychological tests					
– BRIEF-A – MoCA – Stroop test – Working memory tasks	x		x	x	x
	x		x		
	x		x		
	x		x		
Questionnaires					
– Substance use, mental distress, sleep quality, quality of life	x		x	x	x
– IPAQ	x		x		

* SUD diagnosis (i.e. primary substance of use), comorbidities and therapeutic hours. SUD, Substance use disorder; V˙O_2max_, Maximal oxygen uptake; BRIEF-A, Behavior rating inventory of executive function-adult; MoCA, Montreal cognitive assessment; IPAQ, International physical activity questionnaire.

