### Study design and participants

2.1.

This study is a parallel-group RCT (superiority trial) initiated and coordinated by the Clinic of Substance Use and Addiction Medicine (CSAM), St. Olavs Hospital, Trondheim, Norway. Patients with SUD will be recruited from the department for inpatient treatment at Blue Cross - Lade Addiction Treatment Center (Lade ATC), Trondheim, Norway (inclusion and exclusion criteria see Figure 1). Eligible patients will be stratified for primary substance of use (i.e., alcohol or other) and randomized 1:1 to either aerobic HIIT + TAU, or TAU alone (Figure 2). The Clinical Research Unit of Central Norway will provide a block randomization with the software WebCRF3. Recruitment and testing of participants will be carried out by research staff affiliated CSAM, as will the supervision of the HIIT exercise sessions. Therapists and research staff at Lade ATC will inform the patients about the study after an initial detoxification phase. The research staff will then schedule to meet with the patient to provide detailed information, and schedule baseline assessments as soon as the patient has agreed to participate and has signed the written consent form. All testing and training sessions will be performed on-site at Lade ATC. Most patients are hospitalized for 8–12 weeks and will, thus, be recruited for eight weeks. Also, eight weeks of HIIT have been shown to significantly improve aerobic fitness in patients with SUD (41), and to improve executive function in healthy individuals (43).

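### Allocation is stratified by primary substance, but no stated model of the treatment effect includes that factor; adding it with its time interaction is a free, possibly small, gain in precision

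*Protocol article*

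**What the plan says.** On allocation, the section Study design and participants states: "Eligible patients will be stratified for primary substance of use (i.e., alcohol or other) and randomized 1:1". The Clinical Research Unit "will provide a block randomization with the software WebCRF3"; no block size is given.

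On the primary analysis, Sample size and statistical analyses sets out a two-level linear mixed model, "with BRIEF-A score as dependent variable, time point as level 1 and participant as level 2", and then names its terms: "Group allocation and an interaction term between group allocation and time point will be included as covariates". Similar analyses are planned for the secondary endpoints, so the same terms carry over to them.

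Two sentences give the adjustments. The first reads: "In sensitivity analyses we will adjust for baseline values of cardiorespiratory fitness (27), and psychological distress (i.e., SCL-10 total score) (6"). The second concerns ADHD, anxiety and mood disorders: "due to high co-occurrence of those disorders among patients with SUD (81, 82), these will also be adjusted for". Primary substance is in neither.

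Substance type does appear among the secondary aims: "Map CF in subgroups of patients with SUD (e.g. type of substance, age, fitness level"). The abstract says much the same. This describes cognitive function by subgroup and does not adjust the comparison between arms.

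**The concern.** Stratified blocks keep the arms balanced on primary substance. Any difference between alcohol and other users in how BRIEF-A changes is therefore largely removed from the true sampling variation of the treatment contrast. A model without the factor still counts that difference as unexplained variation. Its standard error, confidence interval and p-value then describe a less precise trial than the one that was run.

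At stake is precision. The article names five adjusters (fitness, distress, ADHD, anxiety, mood disorders) but leaves out the one factor that it chose to control by design. The trial is sized with little to spare, so precision that needs no extra participants is worth having. There is also a conditional benefit under the missing-at-random assumption that the article relies on. If dropout depended on substance, and substance predicted change, that assumption would be easier to defend with substance in the model.

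**Working it through.** **Inputs from the article.** Two strata, 1:1 allocation, blocks; Cohen's d = 0.6; power 0.8; significance level 0.05; 45 evaluable per arm.

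**Assumptions, not in the article.** The stratum difference in mean change, D, in within-stratum SD units: 0.3, 0.5 or 0.8. The share of participants in one stratum: p = 0.5, which gives the largest effect for a given D. Blocks of 4 in the simulations.

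**Step 1. The plan's own figure.** By normal approximation, n per arm = 2 × ((1.960 + 0.842)/0.6)² = 43.6, so 44. The noncentral t calculation gives 45 (power 0.804). The stated 45 is reproduced with a two-sided test.

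**Step 2. Does a stable level difference matter?** In a group-by-time contrast, a constant difference between strata cancels. Mixed models were fitted to simulated trials of 110 participants in which the strata differed by 0.8 SD in level but not in change:

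- Complete data: mean standard error of group-by-time 0.1900 without the stratum and 0.1900 with its main effect; the estimates were identical to rounding error.
- 20% of post-tests missing: 0.2098 without and 0.2093 with the main effect.

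A level difference therefore costs essentially nothing, and a main effect alone recovers essentially nothing.

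**Step 3. If substance predicts change.** With balanced strata:

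- Standard error ratio, unadjusted to adjusted: k = √(1 + D²p(1 − p))
- True type I error without the factor: 2 × (1 − Φ(1.96k))
- Precision lost, as a share of the sample: 1 − 1/k²

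| D | k | Type I error | Precision lost |
|---|---|---|---|
| 0.3 | √1.0225 = 1.011 | 4.75% | 2.2% |
| 0.5 | √1.0625 = 1.031 | 4.3% | 5.9% |
| 0.8 | √1.16 = 1.077 | 3.5% | 13.8% |

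Simulation of stratified blocked trials with 45 per arm and no treatment effect agrees. Type I error without the factor was 4.8% at D = 0.3, 4.1% at D = 0.65 and 2.9% at D = 1.0. With the factor it was 5.1% in each case.

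**Step 4. Power at 45 per arm.** Let R² be the share of the variance of change that the stratum explains. With d = 0.6 in units of the total SD within arms, normal approximation:

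| R² | Power without stratum | Power with stratum and its time interaction |
|---|---|---|
| 0 | 81.2% | 81.2% |
| 0.05 | 81.8% | 83.2% |
| 0.10 | 82.5% | 85.1% |
| 0.20 | 83.9% | 88.9% |

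The three values of D correspond to R² = 1 − 1/k² = 0.02, 0.06 and 0.14.

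The scale matters. If 0.6 were instead in within-stratum SD units, power without the factor would be Φ(0.6/√(2/45) − 1.96k) = 80.6%, 79.6% and 76.9% for D = 0.3, 0.5 and 0.8, against 81.2% with it. The article does not say which SD is meant. An ordinary two-group calculation, which reproduces the 45, uses the SD within arms across strata, so the table is the natural reading.

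**The case against.** The strongest case against is that the stated analysis is valid and the gain may be nil. That stands. Nothing in the article says that substance type predicts change in BRIEF-A. The subgroup aim concerns cognitive function itself, in a list of examples, and not change over eight weeks. The assumed range is also generous: equal strata give the largest effect, and a D of 0.8 SD exceeds the 0.6 expected of the intervention.

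The analysis plan is not shown and might add the factor. That stands in part. The article does more than stay silent, however: it names the model terms and the adjusters, and as stated those lists do not match the design.

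A reader might infer more than the article supports:

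- **That no analysis uses substance type.** It is a planned descriptive subgroup variable; it is absent only from the models of the treatment effect.
- **That the standard error is wrong regardless.** It is affected materially only if substance predicts change; a stable difference in level cancels.
- **That false positives rise or the estimate is biased.** The error is in the cautious direction, with type I error at or below 5%.
- **That the trial is underpowered as a result.** The sample size assumed no gain from stratifying, and on the natural reading of d the stated 80% is met without the factor.

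**Conclusion.** The mismatch between the stratified design and the stated models is real. Its consequence is a standard error that is conservatively too large by 1% to 8% over the assumed range of D, and by nothing if D is zero. These sizes rest on equal strata and on values of D that the article does not supply. The statement that planned power stands rests on d = 0.6 being in units of the SD within arms. This is a modest improvement in precision, worth making because it is free. It is not a defect that invalidates the primary analysis.

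**What to change.** Add primary substance (alcohol or other, as recorded at randomisation) and its interaction with time to the primary mixed model, and do the same in the secondary models that compare arms over time. State this before any outcome data are compared by arm. Include the interaction, because the main effect alone leaves the standard error of the change contrast almost unchanged.

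The cost is analysis wording and, with two strata, one main-effect term plus its time interaction. The variable already exists in the randomisation system. Sample size, assessments and conduct are unaffected.
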